## 7.2 Enrollment

After meeting the general inclusion and exclusion criteria, written informed consent must be obtained before the pre-procedure angiography. The angiograms acquired just before the intended procedure (i.e. the pre-procedure angiography) will be used to assure by visual assessment that the reference diameter(s) is  $\geq 2.5^*$  mm and  $\leq 4.0$  mm and the lesion length  $\leq 28$ mm.

\*expanded to 2.25 in diameter when 2.25 mm stent available

Once the angiographic inclusion criteria have been confirmed, the patient should be registered / randomized via the IVRS system.

Due to phased start-up of the clinical sites and to allow all sites to have the opportunity to enroll patients in the study, sites may be asked to delay further recruitment once they have enrolled 50 patients in the SPIRIT Women Single Arm Study and 45 patients in the randomized sub-study.

### **7.3 Procedure**

#### **7.3.1 Medications**

During the procedure, patients will receive appropriate anticoagulation and other therapy according to standard hospital practice. Either unfractionated heparin or bivalirudin may be used for procedural anticoagulation. The use of Glycoprotein IIb/IIIa inhibitors is left to the discretion of the investigator.

#### **7.3.2 Baseline Angiography**

The angiogram acquired during the index procedure (i.e. the baseline angiography) will be assessed visually and parameters will be documented in the eCRF.

#### **7.3.3 Stenting Procedure**

##### **7.3.3.1 SPIRIT WOMEN Single Arm Study**

Once the general and angiographic inclusion and exclusion criteria have been confirmed, the patient should be registered via the IVRS registration system before the placement of the first stent.

Treatment of target lesion(s) should be with either a single stent or planned overlapping stents.

Prior to use, the XIENCE V EECSS should be inspected and prepared according to the Instructions for Use (IFU). All XIENCE V EECSS should be delivered and deployed per the IFU.

All the target lesion(s) should be treated by stenting with the XIENCE V EECSS.

##### **7.3.3.2 Randomized Sub-study**

Baseline angiography of the target vessel will be completed as per the Angiographic Core Laboratory Guidelines.

Once the general and angiographic inclusion and exclusion criteria have been confirmed, the patient should be randomized via IVRS randomization service prior to the placement of the first stent.

Prior to use, the XIENCE EECSS should be inspected and prepared according to the Instructions for Use (IFU). All XIENCE EECSS should be delivered and deployed per the IFU.

All CYPHER SELECT™ Plus Sirolimus-eluting Coronary Stent use should be according to its IFU.

All target lesion(s) should be treated by stenting with the stent assigned per randomization, either XIENCE EECSS or CYPHER SELECT™ Plus Sirolimus-eluting Coronary Stent.

Treatment of target lesion(s) should be with either a single stent or planned overlapping stents.

### 7.3.4 Treatment Rules for the XIENCE EECS

The treatment strategy will be determined by the investigator. It is recommended that each enrolling investigator review the most recent XIENCE IFU to assess contraindications, warnings, and precautions for treating potential patients.

### 7.3.5 Angiography Following Stent Placement

In all patients, an angiographic imaging will be performed immediately following stent placement. Post-stenting images should be captured in the same manner as was used for the pre-procedure images.

For patients enrolled in the randomized sub-study, the procedure should be performed according to the angiographic core laboratory guidelines.

### 7.3.6 Bailout Procedures

Bailout procedures may be performed if the patient experiences any of the following during the index procedure:

Major dissection (type C or greater)

Occlusive complication as evidenced by a decrease in target vessel flow

Chest pain or ischemic ECG changes that do not respond to repeat balloon inflations, medical therapy or lytic agents

Unplanned additional stent is required to cover the target lesion

**SPIRIT WOMEN Single Arm Study:** If bailout stenting is necessary, a XIENCE V EECSS of appropriate length should be used.

**Randomized sub-study:** If bailout stenting is necessary, the stent used should be the same as allocated by randomization for the index procedure and should be used according to the Instructions for Use (IFU).

**IMPORTANT:** For the XIENCE EECSS it is recommended that bailout stent should be placed so that there is no visible gap between the stents. In such a case, at least 1 mm (minimum) to 4 mm (maximum) overlap is recommended.

A bailout procedure is not considered an endpoint event unless the patient sustains death, emergent CABG or MI. Bailout procedures should be avoided unless required for safe patient management. If the bailout procedure was a result of an adverse event/serious adverse event, an appropriate electronic Case Report Form (eCRF) must be completed for this event.

## 7.4 Post-Procedural Testing and Medications

Following the procedure, all patients will be treated in accordance with the hospital standard of care.

### 7.4.1 ECG

.An ECG must be taken within the post-procedure hospitalization period for all patients.

### 7.4.2 Cardiac Enzymes and Creatinine

Routine hospital blood-work and testing should be taken / performed per hospital standards for patient management and must include at least the following:

#### **7.4.2.1 XIENCE V SPIRIT WOMEN Single Arm Study (Local Laboratory)**

One sample for CKMB or Troponin I/T must be taken in the post-procedural hospitalization period, but no later than 24 hours after the procedure.

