### **Additional treatment strategy for patients enrolled in the Single Arm Study is as follows:**

After meeting the general and angiographic inclusion and exclusion criteria, the target lesions should be treated by stenting with the XIENCE V EECSS according to the IFU.

Registration should only be done after confirmation of the angiographic inclusion criteria and before implantation of the first stent.

All lesions should be planned to be treated with the XIENCE V.

If any staged procedures are planned at baseline, it is necessary that the investigator treats the enrolled patients with only XIENCE V EECSS during the planned staged procedure.

Bailout stenting should be performed with XIENCE V EECSS of appropriate length.

It is recommended that all patients should receive  $\geq 75$  mg of aspirin daily for a minimum of five years following the procedure.

It is recommended that treatment with clopidogrel should be continued at 75 mg daily for a period of at least 6 months. Ticlopidine at a dose standard with hospital practice may be substituted for clopidogrel, as required by hospital practice or if the patient develops hypersensitivity to clopidogrel.

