### **Additional treatment strategy for patients enrolled in the randomized sub-study is as follows:**

The test devices used are the XIENCE V Everolimus Eluting Coronary Stent System (XIENCE V EECSS) and the XIENCE PRIME Everolimus Eluting Coronary Stent System (XIENCE PRIME EECSS).

After meeting the general and angiographic inclusion and exclusion criteria, the target lesion(s) should be treated according to the same randomization schedule. If two or more target lesions are to be treated, all lesions must receive the treatment that has been assigned as per the randomization.

If two or more target lesions are to be treated and the patient is randomized to the XIENCE EECSS, all lesions must receive either the XIENCE V EECSS or the XIENCE PRIME EECSS.

Randomization should be done only after confirmation of the angiographic inclusion criteria and before implantation of the first stent. Once randomization is completed and a treatment is assigned, crossover is not permitted.

If it is not possible to implant the stent allocated by randomization, it is recommended that any other commercially available stent, either BMS or DES be implanted, rather than the XIENCE or the CYPHER SELECT™ Plus Sirolimus-eluting Coronary Stent.

If bailout stenting is necessary, the stent used should be the same as allocated by randomization for the index procedure, and should be used according to the Instructions for Use (IFU).

If any staged procedures are planned at baseline, it is necessary that the investigator treats the enrolled patients with the same study stent during the planned staged procedure as was used at baseline (as allocated at randomization).

All patients should receive  $\geq 75$  mg of aspirin daily for a minimum of five years following the procedure.

All patients should receive clopidogrel 75 mg daily for a period of at least 6 months. Ticlopidine at a dose standard with hospital practice may be substituted for clopidogrel, as required by hospital practice or if the patient develops hypersensitivity to clopidogrel.

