## **5 ENDPOINTS**

### **5.1 Primary Endpoint**

The following primary endpoint will be examined:

Adjudicated Composite rate of all Death, all Myocardial Infarction (MI) and Target Vessel Revascularization (TVR) at 1 year.

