#### **7.1.2 Laboratory Assessments**

Routine hospital blood-work should be taken for all patients per hospital standards for patient management. Additional samples for local (all patients) and central laboratory measurements (for patients enrolled in the randomized sub-study) must be taken as described below.

The following laboratory assessments must be obtained within 7 days prior to the index procedure:

| Local laboratory for all patients                                 | Central laboratory for patients enrolled in randomized sub-study |
|-------------------------------------------------------------------|------------------------------------------------------------------|
| Creatine kinase myocardial-band isoenzyme (CK-MB) or Troponin I/T | Creatine kinase myocardial-band isoenzyme (CK-MB)                |
| Pregnancy test (if applicable)                                    | Total Cholesterol, HDL, LDL, triglycerides                       |
|                                                                   | High-sensitivity C-reactive protein (hs-CRP)                     |
|                                                                   | Glycosylated hemoglobin (HbA 1c )                     |
|                                                                   | 17 $\beta$ -estradiol                                            |
|                                                                   | Estrone                                                          |
|                                                                   | FSH level                                                        |
|                                                                   | Free Testosterone                                                |
|                                                                   | Dehydroepiandrosterone (DHEA)                                    |
|                                                                   | Androstenedione                                                  |
|                                                                   | Sex Hormone Binding Globulin (SHBG)                              |
|                                                                   | Homocysteine                                                     |
|                                                                   | Creatinine                                                       |

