#### **Clinical Procedure Success**

Successful delivery and deployment of the study stent or stents at the intended target lesion and successful withdrawal of the stent delivery system with attainment of final residual stenosis of less than 50% by visual estimation, using any adjunctive device without the occurrence of cardiac death, MI attributed to the target vessel and/or CI-TLR during the hospital stay with a maximum of first seven days post index procedure. In multiple lesions setting each lesion must meet clinical procedure success.

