## Myocardial Infarction (MI)

Myocardial Infarction Classification and Criteria for Diagnosis is defined by the Academic Research Consortium as follows:

| Classification      | Biomarker Criteria*                                                                           | Additional Criteria                                                                                                                                               |
|---------------------|-----------------------------------------------------------------------------------------------|-------------------------------------------------------------------------------------------------------------------------------------------------------------------|
| Periprocedural PCI  | Troponin > 3 x URL or CK-MB > 3 x URL                                                         | Baseline value <URL                                                                                                                                               |
| Periprocedural CABG | Troponin > 5 x URL or CK-MB > 5 x URL                                                         | Baseline value <URL and any of the following: new pathologic Q waves or LBBB, new native or graft vessel occlusion, imaging evidence of loss of viable myocardium |
| Spontaneous         | Troponin > URL or CK-MB > URL                                                                 |                                                                                                                                                                   |
| Sudden death        | Death before biomarkers obtained or before expected to be elevated                            | Symptoms suggestive of ischemia and any of the following: new ST elevation or LBBB, documented thrombus by angiography or autopsy                                 |
| Reinfarction        | Stable or decreasing values on 2 samples with a 20% increase 3 to 6 hours after second sample | If biomarkers increasing or peak not reached then insufficient data to diagnose recurrent MI                                                                      |

URL = Upper Reference Limit (defined 99th percentile of normal reference range);

LBBB = Left Bundle-branch Block

\* Baseline biomarker value requiring before study procedure and presumes a typical rise and fall

- **Periprocedural MI After PCI**

The periprocedural period includes the first 48 hours after percutaneous coronary intervention.

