**Planned Staged Procedure**

A planned staged procedure is defined as the treatment of baseline lesions during additional cardiac catheterization procedures following the index procedure. The definition is limited to procedures that are planned during/prior to index procedure. If worsening/exacerbation of patient condition occurs at the time of staged procedure or leads to rescheduling of the staged procedure, or a new clinical condition occurs during the staged procedure, the condition should be reported as an adverse event. The treatment of the baseline lesions at staged procedure will not be considered as a revascularization.

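### Cardiac markers are not clearly required around planned staged PCI, so silent enzyme-defined MI after staging is found only where local practice looks for it, and the procedure-success window does not fit lesions staged later

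*Protocol*

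**What the plan says.** The primary endpoint (Section 5.1) is the "Adjudicated Composite rate of all Death, all Myocardial Infarction (MI) and Target Vessel Revascularization (TVR) at 1 year", so every adjudicated MI in the first year counts.

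Section 4.2 provides for planned staging in both parts. In the single arm study the investigator "treats the enrolled patients with only XIENCE V EECSS during the planned staged procedure"; in the randomized sub-study the investigator "treats the enrolled patients with the same study stent during the planned staged procedure as was used at baseline". Appendix II defines a planned staged procedure as "the treatment of baseline lesions during additional cardiac catheterization procedures following the index procedure". The same entry takes staged treatment of baseline lesions out of revascularization. It makes no such exception for MI.

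Appendix II defines PCI-related MI by troponin or CK-MB above 3 times the upper reference limit (URL), with a baseline value below that limit. On timing it says "The periprocedural period includes the first 48 hours after percutaneous coronary intervention", with no restriction to the index PCI.

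The sampling rules are these:

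- Before the procedure (Section 7.1.2): "The following laboratory assessments must be obtained within 7 days prior to the index procedure". Footnote 1 of Appendix V repeats the link to the index procedure.
- After the procedure, single arm study (Section 7.4.2.1): "One sample for CKMB or Troponin I/T must be taken in the post-procedural hospitalization period", within 24 hours.
- After the procedure, randomized sub-study (Section 7.4.2.2): two samples, the second 3 to 6 hours after the first and within 24 hours.
- Appendix V has no column for a staged procedure, and its CK-MB/troponin row is empty under every follow-up and under additional visits. Section 8.1.1 lists no markers either.

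Clinical Procedure Success (Appendix II) needs success at each lesion and freedom from specified events "during the hospital stay with a maximum of first seven days post index procedure". Appendix II also treats any lesion planned for treatment as a target lesion.

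**The concern.** The protocol defines an endpoint event that can occur at a staged PCI but does not clearly require the measurements that define it. Women whose planned stenting is done in one session have a baseline and a post-procedure marker by rule. Women treated in two sessions have them by rule only for the first session. The 1-year rate would then depend partly on local staging and sampling habits. In the single arm and pooled analyses no control arm offsets this, and a larger sample does not remove it.

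Staging is foreseeable: up to four planned stents are allowed, and triple-vessel treatment is one of the features that define the complex-lesion stratum.

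The success endpoint has a related problem. If a target lesion is treated more than seven days after the index procedure, or in a later admission, the event window has closed before that lesion is treated.

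**Working it through.** **Which rules reach a staged PCI**

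| Item | Reaches a staged PCI? |
|---|---|
| Primary endpoint, all MI to 1 year | Yes |
| Periprocedural MI, 48 hours after PCI | Yes, as written |
| Marker before the procedure | No, expressly index only |
| Markers after the procedure | Unclear: the text refers to the procedure without the word index; its place in Section 7 and the layout of Appendix V point to the enrollment procedure |
| Success window | No, counted from the index procedure |

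Even if the post-procedure rule is read to include staged sessions, no fresh baseline is required, so the baseline criterion may not be assessable.

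**The plan's own precision**

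Inputs from Section 9.2: n = 1550, true rate p from 10% to 14%, two-sided 95% interval. Half-width = 1.96 × √(p(1 − p)/n).

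- p = 10%: 1.96 × √(0.10 × 0.90/1550) = 1.49 points.
- p = 14%: 1.96 × √(0.14 × 0.86/1550) = 1.73 points.

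This reproduces the stated 1.5% to 1.7%. The exact interval planned in Section 9.4 gives 1.53 to 1.76 points.

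**Size of a possible shift**

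Shift = s × m × f × (1 − p), where s is the share of women staged, m the enzyme-defined MI rate after a staged PCI, and f the fraction missed. The factor (1 − p) removes women already counted through another event and assumes independence.

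The document gives neither s nor m. Its only related figure is 1.9% in-hospital non-Q-wave MI in the earlier XIENCE V registry (Section 2.1.1), which is not a staged-PCI rate. Assumptions: s = 5%, 10% or 20%; m = 1.9% (borrowed) or 5%; f = 100%; p = 10%.

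| Staged | m = 1.9% | m = 5% |
|---|---|---|
| 5% | 0.05 × 0.019 × 0.90 = 0.09 points (1.3 of 1550 women) | 0.23 points (3.5) |
| 10% | 0.17 points (2.7) | 0.45 points (7.0) |
| 20% | 0.34 points (5.3) | 0.90 points (14.0) |

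Against the 1.49-point half-width, the 1.9% column is 6% to 23% and the largest entry in the 5% column is 60%. If only half of these MIs are missed, every entry halves. For the shift to equal the half-width with everything missed, s × m would have to be 1.49/0.90 = 1.7% (p = 10%) to 1.73/0.86 = 2.0% (p = 14%); for example, 20% staged with a 10% MI rate gives 2.0%.

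**Procedure success**

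No arithmetic is needed. All planned lesions are target lesions, all must succeed, and the window ends at discharge or seven days after the index procedure. For a lesion staged later, the definition does not say whether it is a failure at the time of scoring, is left out, or is judged without its own in-hospital events.

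**The case against.** A reader might infer that MI after staged PCI cannot be scored at all. The documents do not support that. Section 7.4.2 expects blood-work to hospital standards. Worsening at a staged procedure must be reported as an adverse event, related laboratory tests and ECGs are collected (Section 8.1), and the Clinical Events Committee adjudicates all possible MIs. Q-wave MI needs no raised marker, and MI after 48 hours needs no baseline value. What remains exposed is the clinically silent enzyme rise within 48 hours at a site that does not sample routinely. Those other routes need a trigger, and a silent rise provides none.

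A reader might also infer that the post-procedure samples are expressly confined to the index procedure, or that the error can only be downward. Neither is established. Sections 7.4.2.1 and 7.4.2.2 do not use the word index. The MI footnote asks for a baseline before the study procedure, so a pre-index value might be taken as baseline, and a marker still raised from a recent index PCI could then be scored as a new MI. Understatement is the likelier direction, not the only one.

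The primary endpoint is descriptive, the randomized sub-study is judged on in-stent late loss, and both randomized arms follow the same marker rules, so no test decision changes. Events after a staged session still count in the composites at 30 days, 240 days and 1 year. All of this stands and limits the weight of the point. An analysis plan could add scoring detail, but it cannot supply blood samples that were never taken.

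**Conclusion.** The point holds as a gap in ascertainment. Planned staged PCI falls under the periprocedural MI definition, but a baseline marker is expressly required only before the index procedure, and post-procedure markers at staged sessions are not clearly required. The likely result is a modest understatement of the primary 1-year rate: about 0.1 to 0.3 points at the borrowed 1.9% MI rate, and up to about 0.9 points at an assumed 5%. Both figures assume that 5% to 20% of women are staged and that every such MI is missed. All of these values lie inside the planned half-width. The true size cannot be derived from the document, so a stronger statement that the primary rate is materially biased is not supported. The late-loss comparison is untouched.

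The mismatch in Clinical Procedure Success needs no numerical assumption, but it affects only a descriptive secondary endpoint. The change is worth making because it is cheap and removes a dependence on site practice from a rate that the study aims to estimate precisely.

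**What to change.** Reconcile Sections 7.1.2 and 7.4.2 and Appendix V with the MI and staged-procedure definitions. State that the CK-MB or troponin endpoint samples required before and after the index procedure also apply at each planned staged procedure, using the local laboratory, and show this in the schedule of events. This concerns endpoint measurement and changes no treatment rule. In Appendix II, score Clinical Procedure Success for a staged lesion from its own procedure, with the hospital-stay and seven-day limit counted from that procedure.

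The cost is a few extra local blood samples in staged patients, a line in Appendix V and a sentence in Appendix II. The reported MI rate may come out slightly higher.
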